#### 3.6.2 Methods for unblinding the study

Not applicable.

### 3.7 Pre-study, concomitant and post-study treatment(s)

Subjects using cytotoxic drugs will be excluded from the study. Furthermore, the use of recombinant erythropoietin for stimulation of the hematopoiesis is not allowed during the study. Use of tranexamic acid (Cyclokapron) during surgery is allowed if all subjects at the individual clinic are treated in the same way. Other medication, which is considered necessary for the subject's safety and well-being, may be given at the discretion of the investigator(s). The administration of all medication must be recorded in the appropriate sections of the case report form (CRF).

### 3.8 Treatment compliance

To ensure treatment compliance the local study personnel must follow the recommended manuals and the instructions in this protocol for the investigational product.

## 4 MEASUREMENTS OF STUDY VARIABLES AND DEFINITIONS OF OUTCOME VARIABLES

### 4.1 Screening and demographic measurements

The following demographic data will be recorded via a standard Case Report Form (CRF):

- Date of birth
  - Sex
  - Significant medical and surgical history
  - Medication at entry and during the study
  - Type of anesthetics
  - Surgical procedure and approach
  - Weight and height (BMI)
  - Systolic/diastolic blood pressure (mmHg)
  - Body temperature (°C)
  - Heart rate (beats per minute)
  - Intra- and post-operative blood loss (ml);
    - Estimated by investigator
    - Uncompensated red cell blood loss will be calculated using the following formula
- $\text{Red blood cell loss (ml)} = \text{Estimated total body volume (ml)}^{52} \times (\text{Hct pre-op} - \text{Hct post-op})^{53-55}$

## 4.2 Primary outcome variable

### 4.2.1 Allogeneic blood transfusion

#### 4.2.1.1 Methods of assessment

The need of allogeneic blood will be evaluated at 3 hours after surgery and at day 1, 2, 3, 4 after surgery and at discharge. Every transfusion of allogeneic blood during the study period will be registered in the allogeneic transfusion log.

#### 4.2.1.2 Derivation or calculation of variable

Need for allogeneic blood transfusion will be expressed as transfusion rate in percentage, i.e. number of subjects with allogeneic blood transfusion/total number of subjects, and as the total volume amounts (in ml and expressed as units) of allogeneic blood transfused per treatment group. A transfusion index (units per transfused patient) will also be calculated.

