**Outcome variables****Primary outcome variable:**

- Frequency and amount of allogeneic blood transfusion

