## 6.2 Description of outcome variables in relation to objectives and hypotheses

The primary variable, transfusion rate, will be measured as the proportion ( $\pi$ ) of patients in each treatment group that is receiving allogeneic blood transfusion of the total number of patients in each treatment group. The hypothesis to be tested is:

$$H_0 = \pi_s = \pi_c$$

versus

$$H_1 = \pi_s \neq \pi_c$$

Where:

$\pi_s$  = Proportion patients treated with Sangvia® that require allogeneic blood transfusion in addition to Sangvia® transfusion.

$\pi_c$  = Proportion patients in the control group that require allogeneic blood transfusion.

The hypothesis will be tested using the Fischer Exact Test. The hypothesis will be rejected if the p-value is  $\leq 0.05$ .

Secondary objectives will be tested using similar hypotheses. The total and variable specific proportion values for infection rate, use of post-operative antibiotics and adverse events will be tested between the groups using the Fischer Exact Test. Continuous variables (e.g. post-op Hb values) will be compared and tested using the Wilcoxon Rank Sum test. Laboratory blood markers will also be evaluated for changes over time within each treatment group and this change will be tested using the Wilcoxon Signed Rank test.

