## 6.4 Method of statistical analysis

Fischer Exact test will be used to test frequencies of dichotomous response variables. The non-parametric Wilcoxon Rank Sum test will be used to test differences in continuous response

variables between the parallel treatment groups. Wilcoxon Signed Rank test will be used to test differences over time within each treatment group. P-values equal to or below 0.05 are considered as statistically significant.

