## 6.5 Determination of sample size

The primary variable and objective is the base for the sample size calculation. The sample size formula used is referred to in Lachin 1981.

$$N = \frac{(Z_{\alpha} + Z_{\beta})^2 4\bar{\pi}(1 - \bar{\pi})}{(\pi_s - \pi_c)^2}$$

Where:

N = total number of patients

$Z_{\alpha} = 1.96$  ( $\alpha = 0.05$ )

$Z_{\beta} = 1.2816$  ( $1 - \beta = 0.90$ )

$$\bar{\pi} = \frac{\pi_s + \pi_c}{2}$$

An estimation normal use of allogeneic blood of 21% is based on reported values in the literature. It is acknowledged that in revision surgery a higher percentage of allogeneic blood transfusions is seen than in primary total hip replacements. Because revision patients requiring serious bone grafting are excluded, the percentage of revision patients is expected to be just slightly higher than for the average primary total hip. A high number of revision, e.g. a maximum of 30%, in the total group of patients is considered to have limited effect of the total transfusion rate but are accounted for in the 21% assumed for the total group. The expected values of transfusion rate in the Sangvia® group is estimated to lie around 7%. Accordingly, imputing the values for the estimated transfusion rates in the test and control group generates a mean transfusion rate value of 14%. The sample size necessary for detection of this expected difference in transfusion rate frequency is calculated to 260 patients (5% significance level, two-sided hypothesis, 90% power). Additional 40 patients will be included in the study to compensate for drop-out. In summary, 300 patients will be included in total and 150 in each treatment group.

The transfusion rate of bank blood is considered to vary dependent on type and complexity of surgery. Greatest normal use and differences between the groups are expected in the subgroup with medium (surgery duration 1-2 hours) to complex (surgery duration more than 2 hours) surgery complexity why power are considered to be adequate for the planned subgroup analyses in these groups.

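### Amount of bank blood, half of the primary outcome variable, is derived only as a group total and per transfused patient, so it lacks a per-patient comparison between the randomised arms

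*Protocol*

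**What the plan says.** The protocol synopsis (Outcome variables) gives the primary outcome variable as "Frequency and amount of allogeneic blood transfusion". Section 4.2.1.2 then derives three quantities:

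- the transfusion rate, "number of subjects with allogeneic blood transfusion/total number of subjects";
- the amount, "as the total volume amounts (in ml and expressed as units) of allogeneic blood transfused per treatment group";
- an index: "A transfusion index (units per transfused patient) will also be calculated".

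The confirmatory hypothesis in section 6.2 concerns the first of these only: "The primary variable, transfusion rate, will be measured as the proportion". Fisher's exact test is applied to it, and the sample size in section 6.5 rests on it alone, with 21% assumed in the control group and about 7% in the Sangvia group.

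Two general provisions also bear on amount. Section 6.1 promises standard descriptive statistics for every variable unless otherwise stated. Section 6.4 says: "The non-parametric Wilcoxon Rank Sum test will be used to test differences in continuous response" variables between the parallel groups. Neither says whether an untransfused patient enters the analysis of amount as zero or is left out.

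**The concern.** Only the rate has all patients of the arm as its denominator. The index divides by patients who were transfused, and the trial is designed on the expectation that the arms will differ in who those patients are. Randomisation does not make the two transfused subsets comparable, so a difference in the index mixes the effect on blood use with a change in who is counted. The group total avoids that selection, but it depends on arm size and carries no measure of variability.

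Arm size can matter. Section 6.3 bases efficacy conclusions on the per protocol set, from which patients with wrongful bank blood decisions are removed. Such exclusions can leave unequal arms.

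At stake is the amount half of the primary outcome variable. Units and ml also appear among the health economics variables, and the secondary objectives foresee a payer comparison. Section 4.6.1.2 applies no unit costs within the study, so a later user would need resource use per patient.

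**Working it through.** **Inputs.** Rates of 21% and 7% and 150 patients per arm come from section 6.5. The documents give no units per patient, so every unit distribution below is an assumption.

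**The plan's own figure.** N = (1.96 + 1.2816)² × 4 × 0.14 × 0.86 / 0.14² = 258.2, which agrees with the stated 260. No amount enters this formula.

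**Who the index rests on.** Control: 150 × 0.21 = 31.5 patients. Sangvia: 150 × 0.07 = 10.5 patients.

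**How the measures are related.** Units per patient = rate × index. Hence index ratio = (ratio of units per patient) / (ratio of rates). The planned rate ratio is 0.07/0.21 = 1/3, so index ratio = 3 × ratio of units per patient. The index therefore rises if use per patient falls by less than two thirds, stays level at exactly two thirds, and falls beyond that.

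**Example in whole patients, 150 per arm** (31 and 11 transfused, i.e. 20.7% and 7.3%):

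- Control: 20 × 2 + 11 × 4 = 84 units; index 84/31 = 2.71; 84/150 = 0.56 units per patient.
- Sangvia, the 20 two-unit patients spared and one unit saved in each of the other 11: 33 units; index 33/11 = 3.0 (up 11%); 33/150 = 0.22 per patient (down 61%).
- Sangvia, the same 20 spared and nothing saved in the other 11: 44 units; index 44/11 = 4.0 (up 48%); 44/150 = 0.29 per patient (down 48%).

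**Four other assumed distributions**, with the lightest two thirds of would-be transfused patients spared and no saving in the rest:

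| Units among transfused controls | Index, control → Sangvia | Index ratio | Units per patient, control → Sangvia | Ratio | Total at 150 per arm |
|---|---|---|---|---|---|
| 1/2/3/4 in 30/50/10/10% | 2.00 → 2.90 | 1.45 | 0.420 → 0.203 | 0.48 | 63.0 → 30.5 |
| 1/2/3/4 in 20/60/10/10% | 2.10 → 2.90 | 1.38 | 0.441 → 0.203 | 0.46 | 66.2 → 30.5 |
| 2/3/4 in 70/15/15% | 2.45 → 3.35 | 1.37 | 0.514 → 0.234 | 0.46 | 77.2 → 35.2 |
| 1/2/3 in 67/20/13% | 1.47 → 2.40 | 1.64 | 0.308 → 0.168 | 0.55 | 46.2 → 25.2 |

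First row, by hand: the remaining third holds 0.133 at 2 units, 0.10 at 3 and 0.10 at 4, so the index is (0.267 + 0.30 + 0.40)/0.333 = 2.90.

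**Cases where the index does not rise.** Suppose the device saves one unit in every patient who would have been transfused.

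- Last row of the table: the Sangvia index is (1 × 0.20 + 2 × 0.133)/0.333 = 1.40, down from 1.47. Use per patient goes from 0.308 to 0.07 × 1.40 = 0.098.
- Geometric units with a one-third chance of each further unit: the index is 1/(1 − 1/3) = 1.50 before and after, while the rate falls from 21% to 7%.

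**Whether zeros count.** In 3000 simulated trials under the first row of the table, the Sangvia index was higher in 99.8% and the Sangvia total lower in 98.9%. A Wilcoxon test restricted to transfused patients was significantly worse for Sangvia in 80%. The same test on all patients, zeros included, was significant in 92%.

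**The case against.** The strongest reply is that nothing is really hidden. Rate times index gives units per patient (31/150 × 84/31 = 0.56), as does the total divided by the arm size. The index is listed next to the rate and the total, and both show the saving in every example above. It is an additional measure with no hypothesis, test or decision attached. The general provisions in sections 6.1 and 6.4 can also be read as already giving a per-patient summary and a rank test of amount by arm, with the treatment of zeros left to an analysis plan.

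Most of this stands. It rules out any claim that the efficacy reading as a whole is confused. It does not supply what is missing. A mean reconstructed from rate and index has no standard deviation or interval. Section 4.2.1.2 states its own derivation of amount, and that derivation includes no per-patient quantity. The general provisions do not settle whether zeros count, and the simulation shows that the answer can reverse the direction of the test.

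A reader might go further and infer that a working device necessarily makes its own index look worse. The documents do not support that: they contain no units-per-patient data, and the index is level or lower in the two cases where every would-be transfused patient saves a unit. A reader might also infer that the protocol plans to compare the index between arms. It specifies no such test.

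**Conclusion.** The point holds as a cheap improvement to a stated derivation. Amount belongs to the primary outcome variable, but neither of its two derived forms gives a randomised per-patient comparison with a measure of precision. The index can point the opposite way to blood use: under the assumed unit distributions it rises by 11 to 64% while use per randomised patient falls by about 45 to 61%. That size depends on the lighter users being the ones spared and on the remaining patients saving little. At the planned rates, the index stops rising once use per patient falls by two thirds.

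It would be wrong to infer that the primary analysis is compromised. The test of the proportion transfused uses all patients of each group in the analysis set, and neither it nor the sample size depends on amount. With arms near 150 each, the group totals would also show the saving.

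**What to change.** In section 4.2.1.2, define amount as units and ml of allogeneic blood per randomised patient, counting untransfused patients as zero. Report the mean difference between arms with a 95% interval, for example by bootstrap. State that the Wilcoxon rank sum test already planned in section 6.4 is applied to amount in all patients, zeros included. Keep the group total and the index as description within each arm, and say that the index is not compared between arms.

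The cost is one or two sentences and one additional summary. Every transfusion is already recorded in the allogeneic transfusion log, so no new data are needed, and the sample size and primary test stay as they are.

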## 4.3 Secondary outcome variable

### 4.3.1 Post-operative infection rate

Post-operative infection rate will be assessed by using clinical symptoms of infection, SIRS, specific evaluation of wound infection and assessment of CRP and LPC.

#### 4.3.1.1 Methods of assessment

##### Clinical symptoms of infections:

Clinical symptoms of infections according to the classical signs of inflammation, i.e. swelling, redness, pain, heat and loss of function, and as deemed by the investigator will be regarded as an adverse event and registered in the AE log. Clinical symptoms of infection will be assessed at each check up after end of surgery throughout the study period.

##### SIRS:

Presence of systemic inflammatory response syndrome (SIRS) will be evaluated pre-operatively and at 3 and 24 hours after end of surgery. The definition of SIRS is presence of two or more of the following observations

- Body temperature  $>38^{\circ}\text{C}$  or  $<36^{\circ}\text{C}$
- Heart rate  $> 90$  beats/minute
- Respiratory rate  $> 20$  breaths/minute or  $\text{PaCP}_2 < 32$  mmHg
- $\text{LPC} > 12 \times 10^9/\text{l}$  or  $< 4 \times 10^9/\text{ml}$  or  $0.1\%$  immature neutrophils

##### Wound infection:

Wound infections will be assessed at each check up after end of surgery throughout the study period. Ongoing wound infection will be classified as presence of:

- Purulent drainage or other sign of tissue/wound breakdown

and

- Increasing wound pain or tenderness

##### CRP:

The C-reactive protein concentration given in mg/l will be assessed before surgery, at 3, 24 and 48 hours after surgery and at day 4 after surgery. Surgery induced inflammation and a CRP rise above 10 mg/l after 6 hours with a peak value not exceeding 150 mg/l at 48 hours. Postoperative infection will be defined as a maintained a raised CRP level after 48 hours or a secondary increase, i.e. values > 150 mg/l after 48 hours.

#### LPC:

The Leucocyte Particle Concentration given in count of  $10^9/l$  will be assessed before surgery, at 3, 24 and 48 hours after surgery and at day 4 after surgery. A total count will be used as well as an applicable differentiation in percentage of neutrophils, eosinophils, basophils, lymphocytes (B-cells, T-cells, CD4+ (helper) T-cells, CD8+ (cytotoxic) T-cell and Natural Killer cells), monocytes and macrophages. Total LPC values of either higher than  $12 \times 10^9/l$  or lower than  $4 \times 10^9/ml$  will be considered as an indication of postoperative infection.

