| Health status questionnaire                                   |                        |                            |                                                                                   |                                      |                                      |                                      |                                      | X                   | X                          |

Hb = Haemoglobin concentration (g/dl)

Hct/EVF = Haematocrit/Erythrocyte Volume Fraction (%)

Na+ = Sodium (mmol/l)

K+ = Potassium (mmol/l)

TPC = Thrombocyte Particle Concentration (10^9/l)

LPC = Leukocyte Particle Concentration (10^9/l) with applicable differentiation in percentage of neutrophils, eosinophils, basophils, lymphocytes, monocytes and macrophages.

CRP = C-reactive protein concentration (mg/l)

Creatinine = Serum creatinine ( $\mu$ mol/l), GFR = Glomerular Filtration Rate, CCr = Creatinine Clearance (ml/min/1.73m^2)

SIRS = systemic inflammatory response syndrome, i.e. two or more of the following

- Body temperature  $>38^{\circ}\text{C}$  or  $<36^{\circ}\text{C}$
- Heart rate  $> 90$  beats/minute
- Respiratory rate  $> 20$  breaths/minute or PaCP2  $< 32$ mmHg
- LPC  $> 12 \times 10^9/\text{l}$  or  $< 4 \times 10^9/\text{ml}$  or 0.1% immature neutrophils

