#### 4.3.1.2 Derivation or calculation of variable

Each variable will be evaluated and presented separately and an overall post-operative infection rate will also be calculated.

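### The lower leukocyte limit is written per millilitre instead of per litre, so every count meets the LPC infection criterion and one SIRS item; the overall infection rate also draws on early inflammation markers

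*Protocol*

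**What the plan says.** The note to Table 1 and section 4.3.1.1 (LPC) both report LPC in 10^9/l. Section 4.3.1.1 (LPC) then sets two limits: higher than 12 x 10^9 per litre, or lower than 4 x 10^9 per millilitre. A value beyond either limit "will be considered as an indication of postoperative infection". The count "will be assessed before surgery, at 3, 24 and 48 hours after surgery and at day 4 after surgery", and the criterion is not restricted to any of the postoperative times.

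The same pair of limits, in the same mixed units, forms the leukocyte item of SIRS in section 4.3.1.1 (SIRS) and in the note to Table 1. "The definition of SIRS is presence of two or more of the following observations", and SIRS "will be evaluated pre-operatively and at 3 and 24 hours after end of surgery". In both places the leukocyte item also names 0.1% immature neutrophils with no comparison sign.

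The infection rate is assessed from clinical symptoms, SIRS, wound infection, CRP and LPC (section 4.3.1). Section 4.3.1.2 adds: "Each variable will be evaluated and presented separately and an overall post-operative infection rate will also be calculated". Section 6.2 tests the total and the component proportions between groups with Fisher's exact test.

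On CRP, section 4.3.1.1 says: "Postoperative infection will be defined as a maintained a raised CRP level after 48 hours or a secondary increase". A figure of more than 150 mg/l after 48 hours is attached to the end of that sentence.

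**The concern.** There are two separate problems.

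- **Unit.** A limit that decides whether a patient is flagged is wrong by a factor of 1,000, in three places. Applied as written, the LPC component carries no information and SIRS becomes easier to meet than intended. Both are tested between arms.
- **Content of the overall rate.** LPC from 3 hours and SIRS at 3 and 24 hours are measured when a response to surgery is expected. The CRP paragraph allows for surgery-induced inflammation; the LPC and SIRS paragraphs do not. If such markers count towards an overall infection rate, positives that are not infections dilute a true difference between the arms.

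Infection rate is named first among the secondary efficacy outcomes (section 2.2), and the rationale (section 1.2) cites fewer infections with autologous blood. The result is therefore likely to be read as an efficacy claim.

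**Working it through.** **1. The written limit.** Input: 4 x 10^9/ml (section 4.3.1.1, LPC and SIRS; note to Table 1).

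4 x 10^9/ml x 1,000 ml/l = 4,000 x 10^9/l.

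This is 4,000 / 4 = 1,000 times the same number expressed per litre, and 4,000 / 12 = 333 times the protocol's own upper limit. The two limits overlap, so the rule (above 12 or below 4,000) has no gap:

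| LPC (10^9/l) | Flagged as written | Flagged with lower limit 4 x 10^9/l |
|---|---|---|
| 2 | yes | yes |
| 4 | yes | no |
| 7 | yes | no |
| 12 | yes | no |
| 12.1 | yes | yes |
| 30 | yes | yes |

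With a count for all 150 patients per arm, the LPC component is 150/150 v 150/150, Fisher p = 1.

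**2. Effect on SIRS.** The leukocyte item is always met, so SIRS needs one of the other three items instead of two of four. The documents give no item frequencies, so assume independent items, each of the other three with probability p and the per-litre leukocyte item with probability l.

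- As written: P(SIRS) = 1 - (1 - p)^3.
- Per litre: P(SIRS) = l[1 - (1 - p)^3] + (1 - l)[1 - (1 - p)^3 - 3p(1 - p)^2].

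| p | As written | Per litre, l = 0.1 | Per litre, l = 0.3 |
|---|---|---|---|
| 0.1 | 27.1% | 5.2% | 10.1% |
| 0.2 | 48.8% | 14.2% | 21.9% |
| 0.3 | 65.7% | 26.0% | 34.8% |

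**3. Dilution after the unit is corrected.** Assumptions, none from the protocol except the arm size: true infection 10% v 3%; a share q of both arms flagged by inflammation alone, independently of infection; any positive component counts. The arm size of 150 is from section 6.5.

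Observed rate = 1 - (1 - q)(1 - true rate), so the 7-point difference shrinks to 7(1 - q) points. Power uses the normal approximation, two-sided 5%, with pooled variance under the null. For q = 0: mean rate 0.065; null SE = sqrt(2 x 0.065 x 0.935 / 150) = 0.0285; alternative SE = sqrt((0.09 + 0.0291) / 150) = 0.0282; z = (0.07 - 1.96 x 0.0285) / 0.0282 = 0.50, power 69%.

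| q | Observed rates | Difference (points) | Power |
|---|---|---|---|
| 0 | 10.0% v 3.0% | 7.0 | 69% |
| 0.1 | 19.0% v 12.7% | 6.3 | 32% |
| 0.3 | 37.0% v 32.1% | 4.9 | 14% |
| 0.5 | 55.0% v 51.5% | 3.5 | 9% |

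**4. Primary endpoint.** The formula in section 6.5 gives (1.96 + 1.2816)^2 x 4 x 0.14 x 0.86 / 0.14^2 = 258.2, against 260 stated. Only transfusion rates enter it, so nothing above affects it.

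**The case against.** **The slip is obvious.** The reporting unit and the adjacent upper limit are per litre, and under the literal reading the upper limit would be redundant. An analyst would probably read the lower limit per litre. That is likely, and it makes a reported 100% v 100% improbable. It does not make the criterion right: the error is repeated three times, and a decision threshold should not depend on the analyst's correction.

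**Each component is reported and tested separately** (sections 4.3.1.2 and 6.2). This stands. Wound infection has its own comparison, free of SIRS, LPC and CRP. The dilution concerns the overall rate only.

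**How components combine can be left to a statistical analysis plan.** Also fair; section 6.1 foresees that one may be prepared, and the absence of a combination rule is not the finding. The finding is the wrong limit and the use of early inflammation markers as infection components.

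Four stronger readings are tempting but not supported:

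- *Every patient counts as infected overall.* This follows only if any positive component is enough, which the protocol does not state.
- *Ordinary postoperative signs count as infection.* Clinical symptoms are recorded "according to the classical signs of inflammation, i.e. swelling, redness, pain, heat and loss of function", but the same sentence also requires the investigator's judgement.
- *The CRP schedule cannot separate a maintained level from a secondary rise.* Samples at 48 hours and day 4 allow that comparison, and either pattern counts as infection. The CRP rule also tries to set surgical inflammation apart.
- *The composite is biased against the test arm.* Section 1.1 describes mediators in salvaged blood, not patients' LPC or SIRS status, and says that high levels may also lower the risk of infection. No direction of bias is shown.

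**Conclusion.** The lower leukocyte limit is wrong as written in three places. Taken literally, the LPC indication of infection is met by every patient with a count, 100% v 100%, and one of the two required SIRS items is always present. These statements are exact and need no assumption. The resulting inflation of SIRS (27% to 66% as written, against 5% to 35% per litre) rests on assumed, independent item frequencies of 10% to 30%.

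The dilution of the overall rate is real in kind for LPC from 3 hours and SIRS at 3 and 24 hours. Its size is illustrative: 69% power falling to between 32% and 9% depends on an assumed 10% v 3% true difference, equal non-specific flag rates of 10% to 50% in both arms, and an any-component rule.

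Two wording faults remain: the immature-neutrophil item lacks a comparison sign, and it is unclear whether the 150 mg/l figure governs a maintained raised CRP as well as a secondary increase. All of this concerns a secondary endpoint. The primary analysis and sample size stand.

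**What to change.** 1. State the lower leukocyte limit in 10^9/l in the note to Table 1 and in section 4.3.1.1 under both SIRS and LPC.
2. Reconcile the immature-neutrophil item with the definition that the protocol cites, and give it a comparison sign, in the note to Table 1 and under SIRS.
3. In section 4.3.1.2, base the overall postoperative infection rate on wound infection by the protocol's own rule or on investigator-judged infection as in the clinical-symptoms paragraph. Report SIRS, LPC and CRP separately as inflammatory markers, outside that rate.
4. In the CRP paragraph, say whether more than 150 mg/l applies to a maintained raised level as well as to a secondary increase; if not, state the limit for raised.

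These are changes of wording only, since all items are already collected. They should be settled before the arms are compared, so that the rule is not chosen in view of the result. The cost is a lower overall event rate than the wider composite would show.
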